#### Statistical analyses

We will perform all statistical analyses based on the intention-to-treat principle, analyzing all participants according to their randomized treatment and including all of them in the analyses. Although the allocation is by cluster (GPs), inferences will be made exclusively at the patient level. All the analyses will be performed with Stata, version 17 (StataCorp). We will use multiple imputations for dealing with missing data under a missing-at-random framework. The multiple imputations by chained equations procedure will be conducted to obtain at least 20 imputed datasets, and Rubin's rules will be used to combine them (91). To analyze the effect of the intervention on each outcome measure, we will use hierarchical logistic or linear regression models for clustered data. Our primary analysis will be the absolute risk difference in the cumulative incidence of major depression at 12 months of follow-up, adjusted *a priori* for risk of depression at baseline because it is considered strongly predictive of the outcome and thus clinically prognostic (92). Our secondary analyses will include as dependent variables the respective scores for depressive (70) and anxious (71) symptoms, the probability of the onset of major depression in the next 12 months (29), and mental and physical quality of life (69). We will conduct multilevel linear regressions including the GP and time variables as random components, and the variables group, time, the interaction group^*^time, and the respective measurements of the dependent variables at baseline as fixed components. We will calculate standardized mean differences using the margins in Stata. Sensitivity analyses will be conducted: (1) adjusting for those variables unbalanced at baseline between the arms of the trial; (2) performing complete case analysis and adjusting for inverse probability weighting (93) to minimize attrition bias during follow-up. We will evaluate some moderators (age, sex, educational level, anxiety and physical comorbidity, first lifetime depressive episode, and level of risk for depression) and mediators using multilevel structural equation models to describe the causal chain as Kraemer suggests (94). Finally, we will use different definitions of compliance with adherence to the intervention and perform a complier average causal effect analysis (95).

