### Randomized allocation and masking

We conducted a centralized, blinded, and randomized allocation of GPs to the e-predictD intervention + CAU or the active control + CAU group. An independent person from outside the research team performed the allocation through a computer program. This randomized allocation process was stratified by city. All primary care attendees recruited were automatically allocated to the same group as their GPs to avoid contamination bias between patients. To minimize selection bias attributable to GPs in the patient recruitment process, GPs were required to offer participation in the e-predictD study to all primary care attendees who met the selection criteria. During each day of recruitment, the research assistants checked that the latter was fulfilled.

The GPs were not blinded to their assignment to the intervention or active control group; which is common when health professionals implement psychosocial interventions in clinical trials conducted in the real world (55). However, primary care attendees were blinded to their assignment allocation, because they were informed that two interventions (A and B) would be tested to prevent depression and they would be randomly assigned to one of them. In addition, both intervention and active control groups received the same usual care and some type of intervention to prevent depression (see “interventional methods” section), filled in exactly the same self- and hetero-administered questionnaires, and the respective versions of the app that were downloaded on their smartphones had the same appearance. The research assistants who collaborated in the recruitment of GPs and patients and evaluated some outcomes through interviews (only for the Client Service Receipt Inventory (56) and the Composite International Diagnostic Interview, CIDI-depression) (57) were blinded to their allocations. Those who will perform statistical analyses will also be blinded to the intervention and active-control codes in the databases.

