### Data analysis

#### Power and sample size calculation

To calculate the necessary sample size, we estimate that in the control group, there will be an incidence of major depression of 20% in the year of follow-up since we have previously screened the patients at moderate-to-high risk for depression. We also expect that in the intervention group, the incidence of depression will be 11.2% (absolute risk difference = 8.8%; relative risk = 0.56). In the e-predictD study, we expect a greater effect size than in the predictD study because the latter implements a very simple intervention (a 15-min patient–GP interview every 6 months) for the universal prevention of depression; while in the former, the intervention is more intense and personalized and its target population is at a moderate-to-high risk. We assume an alpha error of 5% and a power of 80% for a two-sample Pearson's chi-squared (two-tailed proportion test) and cluster randomized design: 72 GPs (36 GPs for each group) and 10 patients per GP, assuming that the distribution of the cluster will be homogeneous (CV <0.23) (90), and an intracluster correlation coefficient for GPs of 0.04, which was obtained from a previous study (29). Therefore, we would need to recruit 720 patients in total, 360 for each arm of the trial.

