To calculate incremental cost-effectiveness ratios, incremental costs (cost difference between the intervention and comparator condition) will be divided by the incremental health effects (the effect differences between conditions). To calculate the ‘incremental cost-utility ratio’, the incremental effect is the differences in QALYs between conditions. The incremental costs, health effects, and QALYs will be modeled by generalized linear models to account for clustering effects (GP as a random component) and explore the family and correct link of the models (97). All models will be adjusted by their respective baseline values (i.e., QALYs or cost), the individual risk of depression (predictD risk algorithm), and those variables unbalanced at baseline if necessary. The confidence intervals and the plans and cost-effectiveness acceptability curves will be generated with bootstrapping for each imputed data file (97), varying the values of the availability to be paid from € 0 to € 100,000. Sensitivity analyses will be carried out by modifying unit prices and statistical analyses (e.g., using seemingly unrelated regressions), using the average salary instead of the minimum salary and including the loss of productivity.

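### GP randomisation was stratified by city, but no outcome or economic model names city as a term; if cities differ in outcome, standard errors will be somewhat too wide and tests conservative

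*Protocol article*

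**What the plan says.** **Design.** Under Randomized allocation and masking: "This randomized allocation process was stratified by city". The section on general practitioners and primary care centers names six cities.

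**Primary model** (Statistical analyses). A hierarchical model for clustered data, adjusted a priori "for risk of depression at baseline because it is considered strongly predictive of the outcome and thus clinically prognostic". This risk is the predictD-Spain score. Its 11 predictors, listed under Variables and measurements, include Spanish province and SF-12 quality of life.

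**Secondary models** (Statistical analyses). GP and time are random. Group, time, their interaction and the baseline value of the outcome are fixed. City is not listed.

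**Economic models** (Economic evaluation). GP is random, with adjustment for the baseline value, the predictD risk and "those variables unbalanced at baseline if necessary". City is not listed.

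**Imbalance rule.** For clinical outcomes, "adjusting for those variables unbalanced at baseline between the arms of the trial" is sensitivity analysis (1). In the economic evaluation the same idea is part of the main models. Limitation (7) in the Discussion also mentions it.

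**The concern.** Stratifying by city makes the arms alike in their mix of cities, so differences between cities drop out of the treatment comparison. If the model has no city term, those differences stay in the GP-level variance and are counted in the standard error, although the design has already removed them from the estimate. The interval is then wider than it needs to be, and the test rejects less often than its nominal level.

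At stake is precision that the design has already paid for. The trial planned 72 GPs and 720 patients at 80% power and recruited 69 GPs and 633 patients.

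A second, separate matter is how covariates are chosen. Selecting them by observed imbalance, with no list or threshold, lets the covariate set of the main economic models depend on chance. This does not widen standard errors. It leaves the model unfixed until the data are seen.

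**Working it through.** **Inputs from Power and sample size calculation.** Control incidence 20%; intervention 11.2%, difference 0.088; "an alpha error of 5% and a power of 80% for a two-sample Pearson's chi-squared (two-tailed proportion test"; 72 GPs with 10 patients each; intracluster correlation (ICC) 0.04.

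**Step 1: reproduce the plan's figure.** With mean proportion 0.156, the patients per arm before clustering are

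n = [1.96 × √(2 × 0.156 × 0.844) + 0.8416 × √(0.2 × 0.8 + 0.112 × 0.888)]² / 0.088² = 265.7, so 266.

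Design effect = 1 + (10 − 1) × 0.04 = 1.36. Then 266 × 1.36 = 361.8 per arm, against 360 stated. Power at 360 per arm is 79.9%. The plan's sample size reproduces.

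**Step 2: move part of the ICC to city.** The documents give no between-city variance, so the share is an assumption. If city accounts for c of the 0.04, a model with city has design effect 1 + 9 × (0.04 − c). Without city, the standard error is too large by the factor √(1.36 / that design effect), and the true two-sided size is 2 × [1 − Φ(1.96 × factor)].

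| Assumed c | Design effect with city | SE factor if city omitted | Size if omitted | Power with city |
|---|---|---|---|---|
| 0 | 1.36 | 1.00 | 5.0% | 79.9% |
| 0.01 | 1.27 | 1.035 | 4.3% | 82.5% |
| 0.02 | 1.18 | 1.074 | 3.5% | 85.2% |
| 0.04 (extreme) | 1.00 | 1.166 | 2.2% | 90.4% |

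**Step 3: what naming city gains.** The 79.9% is the planning figure. If c is above zero, stratification already shrinks the true variance even when the model ignores city, so the conservative test has slightly more power than planned. Using the true design effect for the sampling variance and 1.36 for the critical value,

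power = Φ{[0.088 − 1.96 × √(0.2633 × 1.36/360)] / √(0.2595 × D/360)},

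where D is the design effect with city. This gives 80.7% for c = 0.01 and 81.5% for c = 0.02. The gain from the city term is then 82.5 − 80.7 = 1.8 points or 85.2 − 81.5 = 3.7 points.

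**Step 4: recruited numbers.** 633/69 = 9.17 patients per GP; design effect 1 + 8.17 × 0.04 = 1.327; 316.5 per arm. By the design-effect formula, power is 75.6% with c = 0, and with city in the model 78.2% (c = 0.01) or 80.9% (c = 0.02). No loss to follow-up is assumed.

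**Step 5: simulation under no effect.** Six cities, 12 GPs per city, 10 patients per GP, stratified 1:1, cluster-level analysis, 8,000 runs per scenario.

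| SD on logit scale (city, GP) | SE ratio, without/with city | Type I error without city | Type I error with city |
|---|---|---|---|
| 0, 0.50 | 1.00 | 5.1% | 5.0% |
| 0.20, 0.46 | 1.02 | 5.1% | 5.6% |
| 0.35, 0.36 | 1.07 | 3.6% | 4.9% |
| 0.50, 0.50 | 1.11 | 3.1% | 5.1% |
| 0.50, 0 | 1.16 | 2.9% | 5.5% |

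The excess width runs from nil to about 16%, always in the conservative direction.

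**Step 6: which models are most exposed.**

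| Model | City | predictD risk (contains province) |
|---|---|---|
| Major depression (primary) | no | yes |
| Economic | no | yes |
| predictD risk as outcome | no | yes, as own baseline |
| PHQ-9, GAD-7, SF-12 | no | no |

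**The case against.** **Province is already in the risk score.** This stands in part. The primary and economic models carry geography through predictD. A single slope on a composite score, with province weights fixed elsewhere, is not the same as free city effects in this trial, so absorption is partial. The gains above also start from an unadjusted chi-squared formula, while the planned primary model already removes some variance through the score. They are therefore upper bounds for these models. The argument does not reach PHQ-9, GAD-7 and SF-12.

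**This detail belongs in the analysis plan.** A condensed article may omit much. Here, though, the article lists the model terms, for the secondary models down to fixed and random components, and city is not among them.

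**Stronger readings that a reader might infer:**

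- That standard errors are certainly too wide. The documents give no between-city variance, and with none the effect is nil.
- That the primary estimate moves with chance imbalance. It does not: its covariate is fixed a priori on prognostic grounds, and imbalance-based adjustment of clinical outcomes is only a sensitivity analysis.
- That leaving baseline PHQ-9 out of the primary model is an error. The standard error is valid without it. Adding PHQ-9 would be an optional gain, probably small because eligibility restricts its range. An assumed incremental R² of 1 to 5% would take planned power from 79.9% to 80.3–81.8%. The PHQ-9 secondary model does include its own baseline.
- That unblinded GPs ("The GPs were not blinded to their assignment to the intervention or active control group") make the matter worse. Selection at recruitment is a separate issue, and the same section requires GPs to offer the study to all eligible attendees, with daily checks by research assistants blinded to allocation.

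**Conclusion.** The point holds as a modest loss of precision. City is the stratification factor and is not a named term in any model. If cities differ in outcome beyond the adjusted covariates, standard errors are too wide and tests conservative. On the assumption that city makes up 0.01 to 0.02 of the ICC of 0.04, the excess is about 3 to 7%, and planned power of about 80% rises to at most 82 to 85%. The primary and economic models would gain less than this, and the PHQ-9, GAD-7 and SF-12 models are the most exposed. Validity is not threatened, since type I error is not inflated.

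The imbalance rule is a separate and smaller fault. It matters mainly in the economic evaluation, where it enters the main models.

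**What to change.** 1. Include city as a fixed effect (five indicators for six cities) in the primary, secondary and economic models.
2. In the main economic models, replace the unbalanced-variable clause with a short list of prognostic covariates fixed before unblinding, for example age, sex and baseline GAD-7. Use the same list for sensitivity analysis (1) under Statistical analyses.
3. Optionally, add baseline PHQ-9 as a continuous covariate to the primary model.

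The cost is wording and a few model terms. All the variables are already collected, and the analyses are still described as to come.

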#### Economic evaluation

The economic evaluation will be conducted from two perspectives: (1) societal, including the costs of all types of health services (direct costs) and the costs that stem from production losses (indirect costs), and (2) National Health System (including only direct costs from Spanish public health services). As stated above, costs will be estimated through a modified version of the Client Service Receipt Inventory (56). Direct health costs will be calculated by multiplying the number of health service units (consultations, hospital days, tests, etc.) by their standard price and the cost of the medication used by multiplying the cost per daily dose (obtained from the Spanish Pharmaceutical Vademecum, http://www.vademecum.es/) by the number of prescription days recommended. Indirect costs consist of the costs of absenteeism from paid work. Costs of work loss will be calculated by multiplying the days on sick leave by the minimum daily wage in Spain according to the human capital approach. In addition, self-reported presenteeism will be assessed using some questions from the World Health Organization Health and Work Performance Questionnaire (96).

The costs of GP training and visits attributable to interventions in both arms will be added. The QALYs will be calculated using the EuroQol-5D-3L (84). Official Spanish tariffs will be used to estimate the utility of health states described by the patients (86) and linear interpolation will be used for transitions between health states.

To calculate incremental cost-effectiveness ratios, incremental costs (cost difference between the intervention and comparator condition) will be divided by the incremental health effects (the effect differences between conditions). To calculate the ‘incremental cost-utility ratio’, the incremental effect is the differences in QALYs between conditions. The incremental costs, health effects, and QALYs will be modeled by generalized linear models to account for clustering effects (GP as a random component) and explore the family and correct link of the models (97). All models will be adjusted by their respective baseline values (i.e., QALYs or cost), the individual risk of depression (predictD risk algorithm), and those variables unbalanced at baseline if necessary. The confidence intervals and the plans and cost-effectiveness acceptability curves will be generated with bootstrapping for each imputed data file (97), varying the values of the availability to be paid from € 0 to € 100,000. Sensitivity analyses will be carried out by modifying unit prices and statistical analyses (e.g., using seemingly unrelated regressions), using the average salary instead of the minimum salary and including the loss of productivity.

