The GP–patient interview has two parts: the first addresses the preparation of the interview and the second is the interview itself. The first part begins when GPs receive notification that one of their patients has been included in the e-predictD study and his/her e-predictD report and respective PPP for depression are available. The GP will be able to access from his/her PCC desktop computer patient's information if consent was given. As stated previously, when the GPs are reading a patient's e-predictD report, they can open pop-up windows that answer two questions: “What does this mean?” and “What can I do?” Each reasoned response is organized and chosen by the DSS through predefined algorithms based on the availability of scientific evidence and adapted to the GP's context. In addition, the GPs are trained to search for biopsychosocial clinical data in their patient's electronic health records, which could be useful to help patients prevent depression. Among others, they will search physical and mental comorbidities (e.g., hypothyroidism, chronic pain, generalized anxiety disorder/panic attacks, and previous depressive episodes), family and social problems (e.g., loneliness, marital, or economic problems), and all types of treatments and interventions (e.g., antidepressants, anxiolytics, beta-blockers, and previous psychotherapies). Depending on the patient's complexity, 5–15 min should be devoted to this preparatory part of the GP–patient interview.

The only GP–patient interview included in the protocol of the e-predictD intervention has as its general objective to discuss the e-predictD report and its respective PPP for depression, build a therapeutic and patient-centered relationship, and help patients prevent depression. This is a semi-structured GP–patient interview whose script and associated objectives are described in Box 2. This GP–patient interview is designed to last an average of 15 min as a longer duration would not be feasible in a real practice setting in primary care (34). All the GPs in the intervention group received practical training to carry out this interview.

Box 2**Table d95e1322:** Semi-structured patient–GP interview to prevent depression.

**Objectives**	**Script examples**
1) Greet and frame	Mrs. X, thank you for coming to this interview. The purpose of this interview is to talk about the depression prevention program that you have started on your mobile, and we will be here for approximately 15 minutes

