The “physical exercise” intervention module aims to reduce sedentary lifestyles in those patients previously identified as sedentary. There is evidence that exercise-based interventions prevent depression and the effect size of psychological and exercise-based interventions could be similar (40). Therefore, if patients have these two alternatives, the impact on the prevention of depression would be even greater, since those patients who are poorly motivated by psychological programs could be more motivated by physical exercise programs and vice versa. Depending on the contexts (age, physical limitations, own resources, etc.) and preferences, patients can select the type of exercise that most motivate them to practice (gymnastics, walking, cycling, dancing, team sports, etc.). In addition, this module offers a set of videos for performing exercises at home. Finally, this module also offers a list of community resources to practice physical exercise in the neighborhood.The “social relationships” intervention module aims to increase interpersonal relationships in those patients who perceive low social support. A few weeks before the start of the e-predictD intervention, the social workers of each PCC collect and update all the community resources available, which include group activities in the neighborhood where the PCC is located and the patient therefore resides. This list and its basic information (name, telephone, web and physical address, activity of interest related to the prevention of depression, and free or payment required) are entered in this intervention module. Patients should choose any of these available community resources and participate in their activities over time. Moreover, patients and GPs could discuss it in the patient–GP interview to help them decide. Social prescription intervention through community resources could improve perceived social support and thus contribute to the prevention of depression (62). When it is identified that a patient has an interest in improving a relationship with another person, in particular, the patient is redirected to the communication skills module and/or problem-solving module when this relationship is perceived as a problem.The “problem-solving” intervention module aims to help people to find solutions to any problem they want to resolve. There is some evidence of the effectiveness of “problem-solving” interventions in the prevention of depression (63, 64). Dysfunctional attitudes, worrying, a negative problem orientation, and perceived control all play a mediating role in cognitive behavioral therapy (CBT) as well as in problem-solving therapy (65). This module provides instruction on how to apply problem-solving strategies. First, the module helps people to define, concretize, and properly communicate the problem. Then, it deals with turning the problem into an objective to negotiate it and reach agreement. People have to recognize what is important to them and what is expendable and can be offered in negotiation. Exercises to apply/practice these strategies are provided, and then, the module requests feedback on practicing those strategies. In addition, this module offers the possibility of connecting with the communication skills, assertiveness, and decision-making modules whenever the person deems it necessary.The “communication skills” intervention module aims to provide instruction on communications skills to people who identify difficulties communicating with others. Patients obtain information regarding the principles of good communication, considering active listening skills and both verbal and non-verbal communication. In addition, they are encouraged to practice communication skills with others in real situations. Frequently, the module provides reminders to work on these skills and requests feedback on practicing those skills. This intervention module is based on some of the techniques used in both CBT and interpersonal therapy.The “assertiveness” intervention module aims to improve communication skills in difficult communicational situations (such as how to say no, make a request, or defend your own ideas and opinions) in people who feel very uncomfortable dealing with these situations. This intervention module provides instruction on identifying assertive sentences and offers situations with different response options and feedback according to each response. It also includes exercises for practicing with difficult communicational situations adapted to the needs of patients, as well as reminders to work on the skill and to provide feedback on the task performed. This intervention module is related to the previous one, but it is focused on this specific communication skill. Working on assertiveness is another technique included in the programs to improve interpersonal relationships offered by CBT and interpersonal therapy.The “decision-making” intervention module aims to help people who have to make these decisions by reflecting on them and considering the advantages and disadvantages of the different options. This module provides instruction on applying the steps of decision-making strategies. First, people are instructed to define and concretize the decision that they want to make. Second, they are trained to identify several alternatives regarding a decision. Then, patients are encouraged to work on their own decisions, reflecting on and analyzing the advantages and disadvantages of the different alternatives. Finally, patients commit to practicing these strategies in a real setting and this intervention module requests feedback on that practice. These strategies are also included in effective CBT for the prevention of depression.The “improving sleep” intervention module is directed to patients who perceive relevant sleep problems. Many people who suffer from depression have insomnia, and insomnia in turn is a risk factor for depression (66). There is also evidence that interventions aimed at improving sleep prevent depression (67). This intervention module provides information about good sleep habits (sleep hygiene recommendations) and encourages people to follow those recommendations. Every week, the program requests compliance with the recommendations. In addition, the module suggests keeping a diary of sleep quality.The “working with thoughts” intervention module aims to reduce automatic negative thoughts and worries. Cognitive change is the most evaluated and involved mediator in the prevention of depression and anxiety (42). This intervention module provides instruction on how to identify and analyze automatic negative thoughts and turn them into positive thoughts. The sequence is as follows: first, learn to understand cognitive bias; second, identify cognitive bias; and third, change any cognitive bias discovered (negative thoughts). Later, a series of activities are carried out to generate positive emotions that replace negative thoughts. Concerning worries, the goal is to analyze and reduce them. Time is allotted for people to learn to identify worrying. Once this has been learned, people analyze their worries ranking them by relevance and priority and reduce them through relaxation exercises, mindfulness, psychoeducation, and monitoring. Patients can prioritize work with certain thoughts and dispense with others (e.g., worry vs. negative thoughts).

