- Healthcare resource use will be evaluated using the Client Service Receipt Inventory (56), which collects information on the use of services, psychotropic drugs, sick leave, and loss of productivity.- Quality-adjusted life years (QALYs) are measured using the EuroQol five dimension questionnaire (EQ-5D-3L) (84, 85). This is a widely used measure of general health and quality of life, which includes five domains that address mobility, self-care, usual activities, pain/discomfort, and anxiety/depression, and three answer options (no problems, some problems, and extreme problems). In addition, it includes a visual analog scale graded from 0 (the worst health status) to 100 (the best health status). Spanish tariffs will be used to estimate the utility of health states described by the patients (86).

The questionnaires and questions self-completed at baseline by the GP participants in both arms of the trial are the following:

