#### Adherence

To improve study adherence, a research assistant will call participants when the following situations occur: (1) participants do not attend the interview with their GPs, (2) participants have not used the app (which means they have not entered any intervention module) after the visit with their GPs, and (3) participants have not self-completed any follow-up questionnaires.

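### The intervention cost rule names only GP training and visits, leaving social-worker time and the extra running cost of the e-predictD app unpriced, so incremental cost is probably understated

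*Protocol article*

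**What the plan says.** All points are in the protocol article.

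- **Patient-level costs.** They come from the Client Service Receipt Inventory, "which collects information on the use of services, psychotropic drugs, sick leave, and loss of productivity" (*Variables and measurements*). It is administered to patients by telephone.
- **Intervention costs.** *Economic evaluation* adds one line: "The costs of GP training and visits attributable to interventions in both arms will be added". According to *The intervention for the control group*, control GPs receive no training and control patients have no initial GP interview. In practice the line is therefore a cost of the intervention arm.
- **Use of the costs.** In the cost-effectiveness ratio, "incremental costs (cost difference between the intervention and comparator condition) will be divided by the incremental health effects". The cost-utility ratio uses the QALY difference as denominator.
- **Sensitivity analyses.** "Sensitivity analyses will be carried out by modifying unit prices and statistical analyses", and also by using the average instead of the minimum salary and by including lost productivity.
- **Inputs described elsewhere.** For the social relationships module, "the social workers of each PCC collect and update all the community resources available" (*The e-predictD intervention modules*). The sections on personalized reports, personalized plans and the monitoring system describe decision support, GP access to patient reports, and monitoring messages, charts and alerts during the study.

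**The concern.** The costing section is specific about the drug-price source, the wage basis, the utility tariff and interpolation between health states. It is equally specific about which intervention costs are added. Compared with the article's own account of how e-predictD is delivered, that list is short.

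The patient inventory cannot fill the gap. The app is free to participants, so its running cost does not reach them, and they do not see the social workers' time.

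Both inputs belong to the intervention arm. Leaving them out lowers the cost difference and makes e-predictD look cheaper relative to control than it is. Cost-effectiveness and cost-utility are a stated objective of the trial. For a programme delivered mainly through an app, the cost of keeping the app running is part of that question.

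**Working it through.** **1. Inputs set against cost lines**

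| Input | Arm | Priced by the stated rule? |
|---|---|---|
| GP training (10 h + 5 h) and protocol interview | Intervention | Yes |
| Social-worker time for resource lists | Intervention | No |
| Decision support, GP portal, monitoring beyond the control app | Intervention | No |
| 52 weekly messages | Control | No |
| Basic app hosting, questionnaire reminders | Both | No, but largely cancels |
| GP preparation, 5–15 min | Intervention | Not stated whether part of the visit |
| Research-assistant calls for a missed interview or unused modules | Intervention | No; may be trial conduct |

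**2. Direction.** Let c be the net unpriced cost per patient, intervention minus control. The two clear intervention-only items stand against one control-only item, the stored weekly messages. So c is very probably above zero, though the documents do not prove it.

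- Incremental cost is understated by c.
- Net monetary benefit at willingness to pay λ is λ × (QALY difference) − (cost difference). It is overstated by c at every λ, whatever the effect.
- With a positive effect, both ratios are too low.

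**3. The planned effect.** The article states no cost figure. The effect used as denominator comes from *Power and sample size calculation*: 0.20 − 0.112 = 0.088, and 0.112 / 0.20 = 0.56, as stated. The sample size also reproduces. Two proportions at two-sided 5% and 80% power need 266 per arm. The design effect is 1 + (10 − 1) × 0.04 = 1.36, and 266 × 1.36 = 361.8, against 360 stated.

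**4. Scale of the shift**

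- Cost per case avoided falls by c / 0.088 = 11.4c. For an assumed c of EUR 10 this is EUR 114; for EUR 50, EUR 568; for EUR 100, EUR 1,136.
- Cost per QALY falls by c divided by the QALY difference. The article gives no QALY difference, so 0.005 to 0.02 is assumed here. For c = EUR 10: 10 / 0.02 = EUR 500 to 10 / 0.005 = EUR 2,000.

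**5. Perspective.** The societal perspective covers all health services plus production losses, so both unpriced items fall within it. The National Health System perspective takes only direct costs of Spanish public health services. Social workers are staff of the primary care centers, so their time falls there too. The article does not say who would pay for running the app.

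**6. GP preparation.** Training is 36 GPs × 15 h × 60 / 360 patients = 90 min per patient, and the interview averages 15 min. Even if preparation were unpriced, it would be 5 / (90 + 15 + 5) = 4.5% to 15 / (90 + 15 + 15) = 12.5% of GP time per patient.

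**The case against.** The strongest reply is that this is a condensed article. The sentence does not contain the word 'only', nothing says that app or social-worker costs are excluded, and a full economic plan may itemise them. This limits how firmly the gap can be asserted. It does not remove it: the article does not leave intervention costing open but states a rule, and that rule falls short of the delivery it describes.

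A reader might infer more than the documents support, in four ways.

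- **That a quarter to a half of GP time is uncosted.** That share comes from 5 / 20 and 15 / 30, and it assumes that a visit is priced at 15 min without preparation. *GP training and the GP–patient interview* says that 5–15 min "should be devoted to this preparatory part", and it describes preparation as the first of the interview's two parts. Preparation may therefore already sit inside the visit cost, and varying the visit's unit price could also cover it. The share ignores the training time as well.
- **That every omission biases both perspectives.** Only social-worker time clearly belongs to the National Health System perspective.
- **That all app costs fall on one arm.** The control arm has its own app version, weekly messages and the same questionnaire reminders. Only the additional functions of the intervention app count.
- **That the adherence calls are a delivery cost.** "a research assistant will call participants when the following situations occur" stands under an aim of improving study adherence. Two of the three triggers can arise only in the intervention arm, but the calls may be trial conduct rather than delivery.

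It is also fair to say that the resource lists are largely a set-up task, that EUR 10 is only illustrative, and that EUR 500–2,000 per QALY is small against the planned willingness-to-pay range of EUR 0 to 100,000. These points bear on size, not direction.

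**Conclusion.** The concern holds in a limited form. As written, the rule leaves social-worker time and the extra running cost of the intervention app unpriced, and no planned sensitivity analysis adds them. Incremental cost is probably understated: for both items in the societal perspective, and at least for social-worker time in the National Health System perspective.

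The direction rests on one assumption, that these two items together cost more than the control-only messages. The effect on the ratios also presumes a benefit of e-predictD; the effect on net monetary benefit does not.

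The size cannot be established, because there are no unit costs and no QALY difference, and it may be small per patient. The EUR 114 for each net EUR 10 is a conversion at the planned effect, not an estimate of the bias.

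**What to change.** Replace the sentence with a list of intervention cost items for each arm, settled before the economic analysis is run:

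- GP training and visits, as now, stating that the visit cost includes the 5–15 min of preparation.
- Social-worker time for compiling and updating the resource lists.
- Per-user running cost of each app version, so that shared costs cancel and only the difference counts.

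Assign each item to the perspective whose payer bears it. State that one-off app development and research-only tasks are outside the base case. Report sensitivity analyses with and without development cost, and with and without the calls for a missed GP interview or unused modules.

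The cost is some wording and the collation of running-cost records, call logs and staff time. The downside is a slightly less favourable ratio and some staff time estimated in retrospect.
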